# Multiform-based Baduanjin exercise prevention and treatment for idiopathic pulmonary fibrosis: study protocol for a randomized controlled trial

**DOI:** 10.1186/s12906-023-03974-1

**Published:** 2023-05-12

**Keywords:** Idiopathic pulmonary fibrosis, Baduanjin, Lung function, RCT

## Abstract

**Introduction:**

In this study, we will combine the traditional Baduanjin with Yijin Jing and Wuqinxi to create an optimized Baduanjin exercise program with three different forms (vertical, sitting, and horizontal) to adapt to idiopathic pulmonary fibrosis (IPF) patients in vairous stages of the disease. The purpose of this study is to explore and compare the therapeutic effects of this multi-form Baduanjin, traditional Baduanjin, and resistance training on lung function and limb motor function in IPF patients. The goal of this study is to prove a novel optimal exercise prescription strategy of Baduanjin exercise for improving and protecting lung function in IPF patients.

**Methods/design:**

A single-blind and randomized controlled trial is used to conduct this study, while the randomization list will be generated using a computerized random number generator and opaque sealed envelopes with group allocation will be prepared. It will be strictly followed to blind the outcome assessors. and until the experiment’s conclusion, participants won’t know which group they are enrolled in. Patients between the ages of 35 and 80 who have stable diseases and have not regularly practiced Baduanjin exercise in the past will be included. They are divvied up into the following five groups at random: (1) The conventional care group (control group, CG), (2) The traditional Baduanjin exercise group (TG), (3) The modified Baduanjin exercise group (IG), (4) The resistance exercise group (RG) (5) The modified Baduanjin exercise combined with resistance exercise group (IRG). Those CG participants only received the usual treatment, while TC, IG, and RG participants exercised 1 h twice a day for 3 months. MRG participants will have a 3-month intervention with 1 h of Modified Baduanjin Exercise and 1 H of Resistance Training for each day. Every week, all groups underwent will supervis one-day training, with the exception of the control group. The Pulmonary Function Testing (PFT), HRCT, and 6MWT are the main outcome variables. The St. George Respiratory Questionnaire and mMRC are used as secondary outcome measures.

**Discussion:**

This study may produce a new Baduanjin exercise prescription that is user-friendly, simple to execute, more targeted, and adaptable. Because it consists of three forms, including vertical, sitting, and horizontal, it is more adaptable to the various disease stages and actual situations of IPF patients and may compensate for the shortcomings of conventional pulmonary rehabilitation and traditional Baduanjin.

**Trial registration:**

Chinese Clinical Trial Registry, ChiCTR2200055559. Registered on 12 January 2022.

## Background

Idiopathic pulmonary fibrosis (IPF) is a worldwide respiratory disease, which seriously affects the quality of life and workability of patients. It is characterized by dyspnea and progressive deterioration of pulmonary function with a poor prognosis. The incidence of IPF increases with age, with the typical onset of dyspnea between 60 and 70 years of age [1, 2]. The pathogenesis of IPF is still unclear, while the lesion site is limited to the lungs. All adults with unexplained chronic labor dyspnea, cough, double basal artery aspirational popping sound, and/or clubbing fingers should be evaluated for IPF [3]. Currently, the incidence of idiopathic pulmonary fibrosis is increasing globally, with an average incidence of 3 cases per 100,000 people per country. According to current data, rates of stomach, liver, testicular, and cervical cancers are comparable [4]. Currently, Pirfenidone or Nintedanib monotherapy is the most effective treatment for IPF. These medications carry certain risks, have limited utility, and the treatment process is fraught with uncertainty. For instance, more than 20% of patients have discontinued Nintedanib due to adverse events such as diarrhea and liver dysfunction. [5]. Innovative therapies and drug combinations hold great promise for the future, and the effects of non-drug interventions, including various physical therapies, have been assessed and reported [6]. Studies have shown that aerobic and respiratory training appears to complement exercise training and improve dyspnea and health-related quality of life in IPF patients [7]. In Laboratory Animal Research, it is suggested that exercise training can reduce lung damage and improve dyspnea in mice with bleomycin-induced pulmonary fibrosis, thereby delaying the development of IPF [8]. The benefits of exercise training for IPF patients have been recognized, and more and more physicians are recommending it. In light of the fact that PR is an effective and safe tool for the management of IPF, an increasing number of physicians recommend that Baduanjin, a traditional Chinese exercise therapy, be utilized in the PR of IPF patients [9]. Nowadays, its indications are gradually expanding due to its functionality and practicability, which emphasizes not only the interaction between body posture and movement but also the harmony of meditation and breathing techniques. To engage in effective physical activity and mental concentration [10].

Preliminary experimental studies indicate that traditional Chinese exercise is a mild, self-healing, and functional exercise that is primarily characterized by isometric contraction, stretching, relaxation, and adjustment of body posture, combined with breathing techniques, with the primary goal of enhancing physical fitness. A meta-analysis revealed that traditional Chinese exercise is a low- to the moderate-intensity form of exercise that is appropriate for middle-aged and elderly patients with IPF and had a positive effect on lung function (improved FEV1 and FEV1/FVC as indicators), exercise capacity, and quality of life (6MWT) [11]. More and more studies attempt to explore this new application of traditional Chinese exercise in the prevention and control of chronic diseases [12]. pulmonary rehabilitation (PR) is an important component of non-pharmacological treatment for patients with IPF, Studies have shown that aerobic and breathing training appears to be complementary to exercise training, and pulmonary rehabilitation can prolong stressful exercise time in IPF patients, and improve dyspnea and health-related quality of life (HRQoL) in IPF patients [13]. However, some studies have demonstrated that routine tests are unnecessary for additional RCTs comparing pulmonary rehabilitation with standard care and that a new subgroup analysis of pulmonary rehabilitation is more appropriate.

Baduanjin is a kind of qigong exercise that originated in ancient China and integrates body and mind. Combining body and mind maximizes physical and mental health [14] and reduces anxiety, depression [15], physical pain, and other uncomfortable symptoms. Baduanjin emphasizes physical exercise and mental concentration, the connection between symmetrical body posture and movement, and breathing in a meditative and harmonious way. In addition, it has low physical and cognitive demands and is an aerobic exercise of moderate intensity that is suitable for home rehabilitation [16]. Based on its characteristics, it is very suitable for patients with pulmonary fibrosis and special groups such as weakened lung function [17] and has better compliance for the prevention and treatment of chronic diseases. Baduanjin exercise can improve exercise capacity, lung function, and quality of life in patients with chronic obstructive pulmonary disease, in part due to its appropriate intensity and pattern of intermittent intensity. Baduanjin could serve as an alternative to current exercise rehabilitation programs [18]. Therefore, it has been widely used in chronic respiratory diseases and other diseases.

Surprisingly few studies have focused on the critically required positions for recovery in IPF patients who, to avoid exertional dyspnea, frequently adopt a sedentary lifestyle, which predictably results in extensive skeletal muscle degeneration, social isolation, and its negative psychological sequelae [19]. The inhaled and exhaled gases of 28 healthy participants are collected for 45 min (15 min in each position) while they performed three different positions (lying, sitting, standing) in random order. It is determined that standing expends more energy than lying down or sitting, and patients with IPF are frequently forced to sit or lie down to avoid shortness of breath due to impaired lung function [20]. Patients with IPF are significantly less active than their age-matched healthy counterparts. As sedentary time increased, its lower daily physical activity led to a significant decline in survival [21]. The traditional Baduanjin has only one standing position, indicating that we must not only develop a pulmonary rehabilitation program that allows IPF patients to exercise while sitting or lying down in addition to standing, but also minimize prolonged sitting or lying down time in order to improve IPF patient survival. Liu et al. develop a simplified Baduanjin exercise scheme.

In this study, three distinct forms of Baduanjin, including sitting horizontally and vertically, are developed to accommodate IPF patients with varying disease severity; each form has its own distinctive characteristics. As an illustration, the seventh form of the vertical Baduanjin is a combination of the traditional Baduanjin and the “tiger rushing” movement in Wuqinxi. During the exercise, the hands are presented in the form of “tiger claws”, raised to the chest with a deep inhalation to make the sound of “si”, and the process of pushing the hands forward with force, accompanied by the exhalation of the gas, “hu” the sound of. Throughout the breathing process, when inhaling, the diaphragm and intercostal muscles contract, causing the anteroposterior, left and right, and superoinferior diameters of the thoracic cavity to increase, and the thoracic volume expands, causing the air pressure in the lungs to be lower than the outside atmospheric pressure, forming an active inhalation movement. When exhaling, the diaphragmatic muscles and external intercostal muscles relax, causing the thoracic volume to shrink and the lungs to retract, causing the air pressure in the lungs to be greater than the outside air pressure, resulting in passive exhalation. The combination of exhalation exercise and inhalation exercise maintains the continuity and patency of breathing. There is experimental evidence to show that when IPF patients are breathing, the activity rate of the diaphragm is lower than that of the healthy control group, especially when taking a deep breath. To achieve the effect of improving pulmonary ventilation [22]. This may fulfill the function of acute oxygen supplementation, which increases supplemental oxygen tolerance and alleviates dyspnea in individuals with idiopathic pulmonary fibrosis who do not have hypoxemia at rest [23]. At the same time, hypoxia may be related to the peripheral skeletal muscle dysfunction observed in IPF patients [24], so in the rehabilitation of IPF patients, hypoxia and skeletal muscle may have a mutual influence rather than an independent relationship. The fifth pose of Sitting Baduanjin is a combination of the traditional Baduanjin and Yijinjing movements of “drawing the knife”. Place one hand on the neck and the other on the waist and perform the exercise with comparable force using both hands. Through the external and internal rotation of the arms, similar to the action of expanding the chest, the intercostal muscles are contracted and the ribs are lifted, causing the anteroposterior, left and right, and superoinferior diameters of the thoracic cavity to expand and contract, delaying the reduction of chest-related muscles. Studies have confirmed that when the thoracic skeletal muscle mass of IPF patients reaches the level of low muscle mass, it is positively correlated with the quality of survival and prognosis of the patients. Therefore, the exercise of the thoracic skeletal muscle can improve the quality of life and the prognosis of patients [3]. The eighth form of horizontal Baduanjin is “bend the knee joint and dorsi-extend the foot joint”, which is to carry out related exercises for the patient’s limb function. During this session, engage the relevant limb muscles by flexing the knee and hooking the foot to prevent and improve muscle atrophy. Modern research has demonstrated that, with regard to skeletal muscle, appropriate exercise training can have an effect on peripheral skeletal muscle strength and limb mobility [25]. Simultaneously, the majority of anti-fibrotic IPF patients died of chronic respiratory failure; skeletal muscle loss is observed in these individuals, but there is no significant weight loss, which displays that preventing skeletal muscle atrophy in IPF patients is crucial [26].

In this study, five randomly assigned groups are combined with different interventions to evaluate their effects on lung function and motor function in IPF. Because the Modified Baduanjin is easy to learn, easy to operate, easy to carry out, simple, safe, and effective, it is necessary to further study the rehabilitation effect of the Modified Baduanjin on IPF patients. We expect the recommended exercise approach to considerably improve lung function, limb movement, quality of life, and psychological function, and to be applicable to the prevention, treatment, and rehabilitation activities of doctors.

## Methods

### Study design

This is a single-blind, randomized controlled clinical trial comparing (1) conventional care, (2) traditional Baduanjin (3) Modified Baduanjin (4) resistance training, (5) Modified Baduanjin, and resistance training. All the participants are from the Department of Respiratory Medicine, The First Affiliated Hospital of Jiangxi University of Traditional Chinese Medicine. On January 12, 2022, the protocol has been registered in the Chinese Clinical Trial Registry (ChiCTR2200055559). The study has been also approved on February 23, 2022, by the Ethics Committee of the First Affiliated Hospital of Jiangxi University of Traditional Chinese Medicine; the approval number is JZFYLL202202230011. All participants will sign informed consent forms in writing.

Subjects will be assigned according to a computer-generated table of random numbers and will be randomly assigned to 5 groups by an independent person who is unaware of the purpose of the experiment and the recruitment process. Sealed opaque envelopes are used to hide randomly assigned numbers to perform blinding. Considering that the intervention in this study has been performed in a motor manner, it is not possible to complete blinds for participants and therapists, so we included an outcome evaluator to keep the blinds going. The time points of the study are in Fig. 1 and the study procedure is shown in Fig. 2. The study protocol has been designed following the Standard Protocol Items: Recommendations for Interventional Trials (SPIRIT) guidelines [27].

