### Sample size

6MWT is the most commonly used outcome indicator in pulmonary rehabilitation (PR) and can be used for sample size estimation. In 6MWT, the minimum difference (miniDIFF) between different groups is 54 m, and the baseline standard deviation (SD) is 57 m. Given a two-tailed 0.05 and a power of 80%, the minimal sample size for each group is 19. To compensate for the expected loss of participants, an adjusted sample size of 27 could be acquired for each group, and 140 patients could be recruited, assuming a roll-out rate of 30%.

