### Randomization and concealed allocation

Prior to the baseline assessment, participants will be randomized into five groups: CG, IG, TG, RG, and IRG. The allocation sequence will use “study randomized” transcendental prior distribution, the random number generator is (https://www.randomizer.org/) online random number generator, and the participation of participant recruitment assessment or not engage in the researchers. Concealed allocation will be achieved using sequentially numbered, sealed, and opaque envelopes kept in security cabinets that can only be opened by specifically authorized staff.

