### Statistical analysis

The SPSS (version 23.0) is used for data management and statistical analysis. The kolmogorov-Smirnov test is used for normality test. The normality data are expressed as mean ± SD, and the skewness data are expressed as median and quartile spacing. An intention-to-treat analysis will be used to assign participants whether or not they complete the intervention. Lost result data will be processed using a mixed-mode approach. Each protocol is then examined, including only patients who completed all outcome measures and followed the intervention protocol. Comparisons of baseline differences between groups will be made using one-way analysis of variance (ANOVA) or nonparametric tests. The training-related effects are evaluated using a 2 × 2 ANOVA (group × time). Differences in each group of variables over time (time effect, from baseline to 3 months) will be assessed using either a paired T-test or a nonparametric test. To detect differences between categorical variables, the Chi-square test will be applied. Bilateral *P* values < 0.05 are considered significant. In addition, the effects of different interventions on Lung function have been found in previous studies, and disease severity may be an important factor. Therefore, in order to investigate differences in effectiveness based on disease severity, a pre-designated subgroup analysis will be conducted.

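### Disease severity is named as a possible influence on outcome, but the stated between-arm model does not adjust for it and no stated feature of the allocation balances it

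*Protocol article*

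**What the plan says.** **Allocation.** Study design: "Subjects will be assigned according to a computer-generated table of random numbers and will be randomly assigned to 5 groups". Randomization and concealed allocation adds that "the random number generator is (https://www.randomizer.org/) online random number generator" and describes sequentially numbered, sealed, opaque envelopes. The abstract also mentions a generated list and prepared envelopes. No section names a block size, an allocation ratio, strata or minimisation, and none says that allocation is simple.

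**Arm sizes.** Sample size works per group, from a 6MWT difference of 54 m with an SD of 57 m. Its starting figure is this: "Given a two-tailed 0.05 and a power of 80%, the minimal sample size for each group is 19". After allowing for 30% loss it says that "an adjusted sample size of 27 could be acquired for each group", with a total of 140.

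**Severity.** Statistical analysis says "disease severity may be an important factor" and announces a prespecified subgroup analysis. Subgroup analyses goes a little further and treats severity as a possible contributor to differences in the outcome measures themselves. The Background and Discussion link the choice of standing, sitting or lying form to severity. The between-arm analysis, given in both Statistical analysis and Data analysis, is a group × time ANOVA with no covariate named.

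**Timing.** Randomization and concealed allocation: "Prior to the baseline assessment, participants will be randomized into five groups". Data collection and management gives the reverse order, with baseline assessments finished before randomisation.

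**The concern.** The plan singles out one prognostic factor and fits the modified exercise to it, but the main comparison does not use it. A subgroup analysis does not fill that gap. It asks whether the effect differs by severity, whereas adjustment asks whether the arms are compared at like severity.

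With five small arms, some pair will often differ visibly in severity by chance. If severity also predicts change over three months, an unadjusted comparison carries avoidable noise. A reader of the baseline table would then want an adjusted analysis that had not been specified in advance.

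The conflict over timing matters here too. Participants are not blinded to an exercise programme, so a severity value measured after allocation is a weaker covariate than one measured before it.

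**Working it through.** **1. The plan's own figures.** Inputs from Sample size: difference 54 m, SD 57 m, two-sided 5%, power 80%.
- Normal approximation: n = 2 × (57 × (1.960 + 0.842) / 54)² = 17.5, so 18 per group.
- Two-sample t-test: 18.5, so 19 per group, with power 81.1%. This matches the plan.
- Loss of 30%: 19 / 0.7 = 27.1. The plan states 27; rounding up gives 28. 5 × 28 = 140 matches the stated total, whereas 5 × 27 = 135.

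The figures reproduce, and 140 corresponds to 28 per arm.

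**2. Chance imbalance in severity with 28 per arm.** The article gives no severe share and defines no severity strata, so 20%, 30% and 50% are assumed. The SD of the severe share in one arm is √(p(1 − p)/28). The expected range of five independent normal values is 2.326 SDs. A simulation of 400,000 trials gives nearly the same result.

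| Assumed severe share | SD per arm | 2.326 × SD | Simulated mean gap, highest to lowest arm | Some pair differs by ≥ 20 points | A given pair differs by ≥ 20 points |
|---|---|---|---|---|---|
| 20% | 7.6 points | 17.6 | 17.4 | 34% | 6% |
| 30% | 8.7 points | 20.1 | 20.0 | 49% | 11% |
| 50% | 9.4 points | 22.0 | 21.9 | 58% | 14% |

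This calculation uses equal arms. The imbalance therefore remains even if the list was blocked, unless it was also stratified by severity.

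**3. What the planned contrast removes.** With two time points, the group × time interaction compares change from baseline between arms. A severity difference already present in baseline 6MWT, and constant over time, cancels. What remains is any relation between severity and change. For the same reason, adding severity to that ANOVA as a main effect only would leave the interaction contrast essentially untouched. It must enter as severity × time, or as a covariate in a model of the 3-month value that also contains the baseline value. Residual variance then falls by the factor 1 − r², where r is the partial correlation of severity with the outcome given its baseline. The article gives no r, so no figure is put on the gain.

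**4. If allocation were unrestricted.** Simulating 140 patients, each with chance 1/5 per arm:
- The SD of an arm's size is √(140 × 0.2 × 0.8) = 4.7. The smallest arm averages 22, and at least one arm falls below 27 in about 99% of trials.
- After random 30% loss, mean pairwise power is 80.6%, against 81.7% with 28 in every arm.
- For the two smallest arms, power is about 73%, against 77%.

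**The case against.** The strongest reply is that this rests on silence in a condensed article. Block sizes, strata and covariates are often kept for the full protocol or analysis plan. A list prepared in advance and placed in numbered envelopes can hold exactly 28 per arm, and a random-number table does not rule that out. This stands. A reader might infer that the arms will be unequal, but the article does not say so.

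A reader might also infer that the trial misses its 80% power. Even under unrestricted allocation, average pairwise power stays at 80.6%. The loss is confined to comparisons among the smallest arms.

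A third inference is that severity imbalance moves the 6MWT comparison by several metres. A gap of 15 points times an assumed severe-to-mild difference of 30 to 60 m gives 4.5 to 9 m. Both inputs are assumptions, and the product applies to 3-month values alone, whereas the planned contrast is of change. Even at face value it is a quarter to a half of the pairwise standard error, 57 × √(2/19.6) = 18.2 m, with 28 × 0.7 = 19.6 completers per arm. That is ordinary chance variation, already reflected in the confidence interval.

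Finally, the remark on severity in Statistical analysis leads to differences in effectiveness, which a subgroup analysis does address. That is fair for that sentence. The Subgroup analyses section, however, speaks of differences in the outcome measures, and there the stated model makes no use of severity.

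**Conclusion.** The point holds as one of precision and of protection against chance imbalance, not of validity. Randomisation without stratification gives an unbiased comparison, and nothing in the article shows that the arms are unequal.

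The plan does name severity as a possible driver of outcome, leaves it out of the stated between-arm model, and states no allocation feature that would balance it. With 28 per arm, the largest gap in severe share averages 17 to 22 percentage points, on the assumption that 20% to 50% of patients are severe. That gap is the largest over ten pairs of arms; a given pair differs by 20 points or more in only 6% to 14% of trials. How much precision adjustment gains depends on how strongly severity predicts change, which the article does not say.

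The contradiction over whether randomisation precedes the baseline assessment needs no assumption and should be settled in the same edit.

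**What to change.** Trial status says that recruitment is complete, so the allocation cannot change. The analysis text can.

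- **Statistical analysis and Data analysis:** prespecify one baseline severity measure already recorded in the lung function tests, for example DLco as a continuous term. Use it as a covariate in the between-arm model for 6MWT and the other non-lung-function outcomes, in addition to the outcome's own baseline value. If the repeated-measures form is kept, enter it with its interaction with time. Lung function outcomes are left out because their own baseline value already carries this information.
- **Study design and Randomization and concealed allocation:** state the allocation ratio and whether the list was blocked or stratified. If strata were used, fit them in the model.
- **Randomization and concealed allocation against Data collection and management:** reconcile the order of randomisation and baseline assessment, and confirm that the covariate was measured before allocation.

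The cost is one degree of freedom for the tested contrast and a few sentences of text, with no new data or patients. The measure should be fixed before the group codes are opened.
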